### Sensitivity analyses

Proteins identified from association analyses may reflect different scenarios, including causation or confounding from population stratification or dynastic effects. Some possible scenarios include: (1) a protein may be a cause of cancer risk, which we define as “forward causation”; (2) an alternative scenario is that the protein identified is causally downstream of cancer liability, which we refer to as “reverse causation”; (3) there is no causal relationship between the protein and cancer and the identified association reflects horizontal pleiotropy, (4) due to population stratification where spurious associations are due to differences in the GWAS population and those that the PRS is calculated on. We will perform various sensitivity analyses to distinguish amongst these scenarios, described below.

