**Methods and analysis:**

PRS will be calculated using the PRS continuous shrinkage approach (PRS-CS and PRS-CSx) for colorectal and lung cancer risk. This methodology utilises effect sizes from summary statistics from genome-wide association studies (GWAS) available for the cancers of interest to generate weights via the continuous shrinkage approach which incorporates the strengths of the GWAS associations into the shrinkage applied. This methodology both improves upon previous PRS methods in accuracy as well as improving cross-ancestry application in the PRS-CSx approach. GWAS summary statistics will be from the Genetics and Epidemiology of Colorectal Cancer Consortium (GECCO) and the International Lung Cancer Consortium (ILCCO). The association between the polygenic risk scores and 2923 proteins measured by the Olink platform in UK Biobank (UKB) participants with protein measures available will be assessed using linear regression under the assumption of linearity in the proteomic data. The proteins identified could represent several different scenarios of association such as forward causation (protein causes cancer), reverse causation (cancer genetic liability causes protein level change), or horizontal pleiotropy bias (no causal relationship exists between the protein and cancer). Forward and reverse Mendelian randomization sensitivity analyses, as well as colocalization analysis, will be performed in efforts to distinguish between these three scenarios. Protein changes identified as causally downstream of genetic liability to cancer could reflect processes occurring prior to, or after, cancer onset. Due to individuals in the UKB having proteins measures at only one timepoint, and because UKB contains a mix of incident and prevalent cases, some protein measures will have been made prior to a cancer diagnosis while others will have been made after a cancer diagnosis. We will explore the strength of association in relation to the time between protein measurement and prevalent or incident cancer diagnosis.

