## Methods and analysis

### Polygenic risk score analyses

PRS can be developed using GWAS summary statistics on the associations of many SNPs across the genome with cancer. In this way millions of SNPs can be combined to develop an individual’s PRS for a cancer. A PRS is the sum of the number of copies of risk alleles individuals have for SNPs across the genome, weighted by the effect size of these SNPs in relation to the disease of interest, in this case, cancer [19]. While the initiation of cancer and the factors that contribute to the onset and progression of cancer are still not fully understood [20]; by calculating a PRS using data from all SNPs across the genome, SNPs involved in initiation, promotion and progression of cancer will be captured by this score, reflecting the complex process of cancer development [18].

In this study, PRS will be calculated for UKB participants (Application ID: 15825/81499) with proteomic measurements (N = 49,542), individuals with sex-mismatch (derived by comparing genetic sex and reported sex) or individuals with sex-chromosome aneuploidy will be excluded from the analysis (N = 814) as well as highly related individuals related to a 3^rd^ degree to >200 individuals (N = 2) [21]. For colorectal cancer, we will use effect weights derived from GWAS summary statistics of the: i) Genetics and Epidemiology of Colorectal Cancer Consortium (GECCO) (GWAS Catalog Accession: GCST90255675) for Europeans; and ii) the Asia Colorectal Cancer Consortium (ACCC)/Korean-National Cancer Centre CRC Study 2 (Korea-NCC2) for GWAS summary statistics for East Asians. For lung cancer, we will use effect weights derived from GWAS summary statistics from the International Lung Cancer Consortium (ILCCO) (GWAS Catalog Accession: GCST004748). Sample selection and quality control within these studies has been previously described [22,23].

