### Olink proteins

Olink protein measurements were performed as part of the Pharma Proteomic Project (UKB-PPP) on blood plasma samples using the antibody-based protein Olink Explore 3072 Proximity Extension Assay. Proteomics were generated for 54,219 participants who were considered to be highly representative of the UK Biobank population on baseline characteristics and showed enrichment for selected diseases [30]. The number of participants with colorectal and lung cancers can be seen in Table 1. Quality control, sample selection and data processing has been described previously [30]. Associations between the participants’ PRS and 2923 Olink protein measures from the UK Biobank will be tested via linear regression, adjusting for age, sex, principal components and sample storage time where this has an impact on protein level variation [31]. Protein measures will undergo inverse rank normal transformation (INT) for each protein [32]. The number of independent proteins will be calculated using the metaboprep R package [33]. False discovery rate correction will be applied to p-values, proteins with p-value less than the calculated alpha will be prioritised for further analyses.

**Table 1 pone.0312970.t001:** Cancer frequency within the UKB cohort and within the UKB-PPP study participants.

ICD10/ICD9 code	Cancer	Number of cases (UKB)	Number of cases (UKB-PPP)
C18/153	Malignant neoplasm of colon	6015 (1.2%)	630 (0.13%)
C19/1540	Malignant neoplasm of rectosigmoid junction	642 (0.13%)	67 (0.013%)
C20/1541	Malignant neoplasm of rectum	2670 (0.53%)	268 (0.053%)
C34/162	Malignant neoplasm of bronchus and lung	5305 (1.1%)	597 (0.12%)
**ICD-O-3 Code**	**Histological Subset**	**Number of cases (UKB)**	**Number of cases (UKB-PPP)**
8140, 8211, 8250–8260, 8310, 8323, 8480–8490, 8550	Lung adenocarcinoma	2390 (0.48%)	261 (0.052%)
8070-8072	Lung squamous cell carcinoma	1244 (0.25%)	151 (0.03%)
8041–8042	Lung small cell carcinoma	502 (0.1%)	64 (0.013%)

Number of cases for each cancer type derived from UK Biobank phenotypic data with percentage of cases out of overall individuals is represented in brackets. UKB overall n = 501939, UKB with protein measures (UKB-PPP) n = 52996.

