#### Assumptions.

The three core assumptions of MR, known as the instrumental variable (IV) assumptions (Fig 2), are relevance (IV1) – is the instrumental variable (G) associated with the exposure (E), independence (IV2) – there is no confounding of the association between the instrument (G) and outcome (O) (this can arise through population stratification, dynastic effects and assortative mating) and exclusion restriction (IV3) – the instrumental variable (G) does not act on the outcome (O) except via the exposure (E) no horizontal pleiotropy (red dashed line, IV3) [37–39].

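### Population stratification is listed among four scenarios the sensitivity analyses are said to distinguish, but none of the analyses described tests it

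*Protocol article*

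**What the plan says.** The Sensitivity analyses section numbers four scenarios for a protein associated with the cancer PRS: forward causation, reverse causation, horizontal pleiotropy, and an association "due to population stratification where spurious associations are due to differences in the GWAS population and those that the PRS is calculated on". It then commits: "We will perform various sensitivity analyses to distinguish amongst these scenarios, described below".

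The abstract names forward and reverse MR and colocalization, and says they "will be performed in efforts to distinguish between these three scenarios". The three it has just listed are forward causation, reverse causation and horizontal pleiotropy.

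The Assumptions section places stratification under IV2, the absence of confounding between instrument and outcome, and says of such confounding that "this can arise through population stratification, dynastic effects and assortative mating".

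The Olink proteins section describes the discovery regression as "adjusting for age, sex, principal components and sample storage time where this has an impact on protein level variation". The number and source of the components are not given.

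On the analysis set, the Polygenic risk score analyses section starts from participants with proteomic data (N = 49,542) and states that "individuals with sex-mismatch (derived by comparing genetic sex and reported sex) or individuals with sex-chromosome aneuploidy will be excluded from the analysis" (N = 814), together with two people who have very many relatives in the cohort. The limitations refer to a European population with sufficient protein data. The sample-selection flowchart, Fig 3, is not available in the text reviewed.

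**The concern.** The plan says its analyses can do something that, as described, they cannot. A reader of the results would take a protein that has come through MR, clustering and colocalization as having been examined for stratification, because the article says that all four scenarios are to be separated.

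The mechanism is familiar. The mean of a polygenic score can differ between ancestry groups for reasons unrelated to disease risk. If the mean of a protein also differs between those groups, a pooled regression shows a slope with no causal content. What is at stake is the interpretation of a surviving hit: the plan has no step whose result would lead anyone to label it scenario 4.

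**Working it through.** **Step 1. Match each analysis to what it addresses.** The targets below are those given in the article.

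| Analysis | Section | Addresses |
|---|---|---|
| Forward and reverse MR | Study design | Direction of effect |
| F-statistic | Instrument & method selection | Weak instruments |
| Cochran's Q, MR-PRESSO, weighted mode, weighted median | Instrument & method selection | Pleiotropy (IV3) |
| RAPS | Instrument & method selection | Pleiotropy, weak instruments, measurement error |
| CAUSE | Instrument & method selection | Correlated and uncorrelated pleiotropy |
| MR-Clust, NAvMix, contamination mixture, PheWAS-based clustering | Instrument & method selection | Distinct pathways, invalid instruments |
| Colocalization | Colocalization | LD confounding at a locus |

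No row is assigned to IV2 or to population structure. The Sensitivity analyses section counts four scenarios to be distinguished and the abstract counts three. The methods described match the abstract.

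**Step 2. Can the ancestry of the analysis set be read from the counts?** Table 1 gives 52,996 participants with protein measures. Removing the listed exclusions gives 52,996 − 814 − 2 = 52,180, which is 2,638 more than 49,542. If 49,542 is instead the number before exclusions, the analysis set is 49,542 − 814 − 2 = 48,726. On either reading the text leaves some filtering undescribed. An ancestry filter can be neither confirmed nor excluded.

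**Step 3. How large could the bias be?** The documents give no figure for this, so every input except N and the number of proteins is an assumption. Take two groups, with a minority share p, a PRS mean shift d and a protein mean shift y, both in within-group SD. Then

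r = p(1−p)·d·y / √[(1 + p(1−p)d²)(1 + p(1−p)y²)], and expected z = r·√N, with N = 49,542 and √N = 222.6.

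The reference cut-off is two-sided 0.05/2,923, z = 4.30. The plan uses false discovery rate control, so its actual cut-off may be lower.

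- Low end (p = 2%, d = 0.25, y = 0.1): r = 0.0196 × 0.025 / 1.001 = 0.0005, z = 0.11.
- Middle (p = 5%, d = 1, y = 0.5): r = 0.02375 / √(1.0475 × 1.0119) = 0.0231, z = 5.13.
- High end (p = 10%, d = 1, y = 0.5): r = 0.045 / √(1.09 × 1.0225) = 0.0426, z = 9.49.

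These apply without component adjustment, which is not the model planned. If the components remove 90% of the between-group covariance, the range becomes 0.01 to 0.95. If they remove 99%, it is at most 0.09.

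**Step 4. What the residual means per protein.** With no shift, the chance that one protein passes |z| > 4.30 is 0.05/2,923 = 1.7 × 10⁻⁵. With an expected z of 0.95 it is about P(Z > 4.30 − 0.95) = P(Z > 3.35) = 4.0 × 10⁻⁴. Even if all 2,923 proteins sat at that extreme, about 2,923 × 4.0 × 10⁻⁴ = 1.2 would pass, against 0.05 with no shift. A residual of this size would be a handful of hits at most, under assumptions chosen at the unfavourable end.

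**The case against.** The strongest reply is that stratification is controlled where it matters, at discovery. Principal components are the standard safeguard, and on the figures above the residual is small. This stands, and it limits the point to a residual risk. It does not answer the gap in the text: a covariate reduces bias in every estimate but does not tell the team which surviving hit, if any, is scenario 4.

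A reader might go further and infer three stronger things. The documents do not support them.

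- *That stratified hits will be passed as causal.* The z values above 4.30 arise only without components. Nor does any section say that a hit unsupported by MR in either direction is called causal.
- *That MR repeats the same bias because it uses the same SNPs.* Forward MR uses cis-pQTLs, not the PRS variants. Reverse MR uses only genome-wide significant SNPs and excludes cis-pQTLs for the protein, so it is not the genome-wide score. An artefact of the score mean need not recur in either.
- *That the sample is unrestricted by ancestry.* The limitations point to a European set, Fig 3 is not shown, and the counts leave filtering undescribed. All that can be said is that no section shown states an ancestry restriction.

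Two further replies have some force. Replication in DECODE and EPIC gives indirect protection, since an artefact specific to UK Biobank is less likely to reappear there, although it is not presented as a check on scenario 4. For colorectal cancer a combined European and East Asian score is also planned, so the scores are not all European-weighted.

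Finally, the number of components and similar detail can reasonably sit in a fuller plan. The point does not depend on that detail. It depends on an explicit claim in the article that its described methods do not meet.

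**Conclusion.** The point holds in limited form. The Sensitivity analyses section promises to distinguish four scenarios, the analyses described address the other three, and the abstract claims only three. This rests on the text alone and needs no assumption.

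The likely bias is residual. On assumed minority shares of 2% to 10% and mean shifts of 0.25 to 1 SD in the score and 0.1 to 0.5 SD in the protein, expected z is at most 0.95 if components remove 90% of the between-group covariance, and at most 0.09 at 99%. How much they remove is itself an assumption, and the two-group illustration does not cover finer structure within one ancestry group.

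It should be corrected, because the correction is cheap and changes what a surviving hit can be said to show. It does not show that the discovery analysis is invalid.

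**What to change.** Choose one of two routes.

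1. **Add a check for scenario 4.** For each protein taken forward, repeat the PRS-protein regression within one genetically inferred ancestry group, with principal components computed in that group and assessment centre added as a covariate. Define in advance what counts as a material change in slope from the main model, and flag proteins that meet it as possibly due to stratification.
2. **Withdraw the claim.** State that stratification is handled only by covariate adjustment in the discovery regression, and remove scenario 4 from what the sensitivity analyses are said to distinguish, so that the section agrees with the abstract.

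On either route, state the ancestry of the analysis set and account for the step from 52,996 to 49,542 in the text.

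The first route costs one repeat run on UK Biobank data for which access has been obtained, with slightly fewer participants in that check and the main estimate unchanged. The second costs a sentence.

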### Bidirectional Mendelian randomisation sensitivity analyses

MR uses genetic variants, associated with the phenotype of interest as the instrumental variable to assess the effect of the phenotype on an outcome. Due to the random nature of inheritance of genetic variants there is an advantage over observational epidemiology whereby confounders may influence both the exposure and outcome of interest [34–36]. Genetic associations used in MR analyses often come from GWAS summary data, whereby association is conventionally defined by a p-value threshold of 5 x 10^−8^.

#### Assumptions.

The three core assumptions of MR, known as the instrumental variable (IV) assumptions (Fig 2), are relevance (IV1) – is the instrumental variable (G) associated with the exposure (E), independence (IV2) – there is no confounding of the association between the instrument (G) and outcome (O) (this can arise through population stratification, dynastic effects and assortative mating) and exclusion restriction (IV3) – the instrumental variable (G) does not act on the outcome (O) except via the exposure (E) no horizontal pleiotropy (red dashed line, IV3) [37–39].

**Fig 2 pone.0312970.g002:**
[figure not shown]
Directed Acyclic Graphs (DAGs) showing the three IV assumptions of Mendelian Randomization. IV1 represents that the assumption that the genetic variant (G) is strongly associated (red arrow) with the exposure (E). IV2 represents the assumption that confounders don’t also act on the genetic variant (red dashed arrow) as they do the outcome. IV3 represents the assumption that the genetic variants do not affect the outcome through other routes separate from the exposure (red dashed arrow) (C).

### Study design

MR will be performed in the forward and reverse direction: forward MR, where the protein is the exposure and cancer is the outcome, will be used to estimate the effect of selected proteins on the cancer of interest and reverse MR, where cancer is the exposure and protein levels are the outcomes, will be used to estimate the effect of cancer liability on circulating protein concentration [17]. Forward MR will be performed using cis-pQTLs to instrument proteins identified as being associated with the cancer PRS, the threshold for these will be p < 3.4 x 10^−11^ [40]. Cis-pQTLs will be defined as within < 1Mbp of the protein coding gene and trans-pQTLs will be defined as > 1Mbp away from the protein coding gene [41]. Reverse MR will be performed using SNPs associated with the cancer PRS at a threshold of p < 5 x 10^−8^ excluding cis-pQTLs for the protein. If association is found in the forward direction this may suggest that the protein is causal for the cancer but if association is found in the reverse direction this may suggest that genetic liability to cancer is causing the protein level change [17]; to elucidate this causality, different MR estimation methods will be employed, the application and conditions of these are described below.

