### Instrument & method selection

The strength of instrument will be determined by calculating the F-statistic, a measure of potential weak instrument bias that could arise from the use of IVs as a proxy for the effect of exposure on outcome [39]. The F-statistic takes into account the genetic variance (R^2^), the sample size and how many instruments are present. An F-statistic greater than 10 indicates that the bias from weak instruments is small, where this F-stat is less than 10 this indicates a possibility of bias and will be noted [42].

Dependent on the number of SNPs available, the appropriate method of effect-estimation will be selected for MR analyses. For proteins with a single pQTL SNP the Wald ratio will be calculated as the ratio of SNP-outcome/SNP-exposure association [43]. For proteins with two or three independent SNPs, a fixed-effects inverse variance weighted (IVW) model will be used. For four or more independent SNPs, a random effects inverse variance (IVW) model, combining multiple SNP outcome/exposure Wald ratio, will be used [44]. In the event of multiple independent SNPs, pleiotropy will be considered by calculating Cochran’s Q statistic, a method for assessing global and individual pleiotropy across instruments [45]. Weighted mode and weighted median methods will also be used when > 10 SNPs are available [46,47].

The MR-PRESSO, weighted mode and weighted median methods will be used to assess IVs for horizontal pleiotropy, violation of IV3 where the IV acts on the outcome not via the exposure, by comparing estimates with and without suspected pleiotropic variants, this will be repeated for both forward and reverse MR [48]. In addition being robust to pleiotropy methods such as MR robust adjusted profile score (RAPS) also accounts for other potential sources of bias such as weak instruments and measurement error in the exposure [49]. MR-CAUSE (Causal Analysis Using Summary Effect estimates) is another method that can be used when IV3 is violated due to pleiotropic effects of correlated pleiotropy, where the pleiotropic factor is a confounder of the exposure-outcome association versus when the IV has effects on pleiotropic factor independently of the effect of the IV on the exposure this is uncorrelated pleiotropy [50].

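### Forward MR sets no condition on protein-altering cis-pQTLs although the assay reads binding, so a forward estimate can have the wrong sign or size or be falsely null, above all with one instrument

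*Protocol article*

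**What the plan says.** The Study design section sets the forward-MR rule: "Forward MR will be performed using cis-pQTLs to instrument proteins identified as being associated with the cancer PRS". Two criteria follow. On strength, "the threshold for these will be p < 3.4 x 10^−11". On position, "Cis-pQTLs will be defined as within < 1Mbp of the protein coding gene". Variants inside the gene, including those that change the protein's sequence, meet the second criterion. The section says that forward MR will estimate the effect of the selected proteins on cancer, and that a forward association may point to a causal protein.

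The Olink proteins section says that the proteins were measured "using the antibody-based protein Olink Explore 3072 Proximity Extension Assay". The Strengths and limitations section concedes that this technology captures binding and not level. That concession is not carried into instrument selection or into the reading of forward MR.

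The Instrument & method selection section supplies the checks. On strength: "An F-statistic greater than 10 indicates that the bias from weak instruments is small". On estimators: "For proteins with a single pQTL SNP the Wald ratio will be calculated as the ratio of SNP-outcome/SNP-exposure association", and "For proteins with two or three independent SNPs, a fixed-effects inverse variance weighted (IVW) model will be used". Four or more SNPs get random-effects IVW. Cochran's Q is planned wherever there are several independent SNPs. "Weighted mode and weighted median methods will also be used when > 10 SNPs are available". MR-PRESSO, RAPS and CAUSE are also named. Colocalization and replication in two other studies have their own sections.

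**The concern.** Forward MR divides a variant's association with cancer by its association with the measured protein. That ratio is an effect of protein level only if the denominator is a change in level. On an antibody-based assay, a variant that changes the protein's sequence can move the readout by changing how well the antibody binds, whether or not the circulating amount changes. The cis window is where such variants lie, and the stated criteria neither exclude nor mark them.

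The sign and size of a forward estimate would be read as the effect of more or less protein on cancer, which bears on its use as a prevention target. A null would be read as evidence that the protein is not upstream, which leaves it as a candidate downstream marker. Either reading can be wrong if the instrument moved binding and not level.

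**Working it through.** The document states no power, error rate or bias figure on this point, so there is none to reproduce. Three checks apply.

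**1. Can the F-statistic flag an admitted SNP?** Input: the threshold p < 3.4 x 10^-11 (Study design), two-sided.
- z = 6.63, so single-SNP F = z² = 43.9 at the threshold and higher below it.
- Every single SNP that is admitted therefore exceeds 10. The check adds nothing to the threshold, and a strong binding effect only raises F.
- Share of readout variance at the threshold, F / (F + N - 2). The size of the pQTL sample is an assumption. It gives 0.089% for N = 49,542 (Polygenic risk score analyses), 0.090% for N = 48,726 (49,542 - 814 - 2) and 0.083% for N = 52,996 (Table 1). A small binding effect is enough to qualify.

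**2. What does the Wald ratio estimate?** Let θ be the true effect of protein level on cancer (log odds ratio per SD), a the variant's effect on true level, b its effect on binding, and f its effect on cancer other than through level. Then

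Wald ratio = (θa + f) / (a + b).

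All values below are assumptions chosen to show the behaviour.

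| θ | a | b | f | Calculation | Ratio | Reading |
|---|---|---|---|---|---|---|
| 0.2 | 0.3 | 0 | 0 | 0.06 / 0.3 | 0.20 | correct |
| 0.2 | 0.3 | -0.5 | 0 | 0.06 / -0.2 | -0.30 | sign reversed |
| 0.2 | 0.3 | -0.2 | 0 | 0.06 / 0.1 | 0.60 | three times too large |
| 0 | 0 | -0.2 | 0.06 | 0.06 / -0.2 | -0.30 | level effect reported where there is none |
| 0.2 | 0 | -0.2 | 0 | 0 / -0.2 | 0 | true level effect missed |
| 0 | 0 | -0.2 | 0 | 0 / -0.2 | 0 | correct null |

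The last two rows set the limit. A variant that changes binding only gives no false signal. Its harm is a false null when the protein is truly upstream.

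**3. Which checks remain, by number of instruments?**
- *One SNP.* Only the Wald ratio exists. Q, MR-PRESSO, weighted median and weighted mode need several SNPs. Colocalization asks whether protein signal and cancer share a causal variant. A variant that changes binding and also affects cancer is shared, so it passes.
- *Three SNPs, one affected.* Assume θ = 0.2, a = (0.30, 0.25, 0.20), b = (0, 0, -0.6). Apparent effects are x = a + b = (0.30, 0.25, -0.40) and cancer effects are y = θa = (0.06, 0.05, 0.04). With equal standard errors, fixed-effects IVW is Σxy / Σx² = 0.0145 / 0.3125 = 0.046, against a true 0.20.
- *Cochran's Q in that example.* The squared residuals sum to 0.00703. At an assumed standard error of 0.02, Q = 0.00703 / 0.0004 = 17.6 on 2 df, p = exp(-17.6 / 2) = 0.00015. At 0.04, Q = 17.6 / 4 = 4.4 and p = exp(-2.2) = 0.11. So Q may flag the artefact, depending on precision. The document states no rule for what follows when it does.

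**The case against.** The strongest reply is that the harm is narrow and largely acknowledged. Most of it stands:

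- A reader might infer that binding artefacts create false upstream labels. The algebra does not support that for a variant that changes binding only, which gives zero. Where the variant acts on cancer by altering the protein's function, the protein is a real cause of cancer, and the article's definition of forward causation carries no sign. The label is then right, and only the claim about level, its sign or its size is wrong.
- A reader might infer that no planned check could reveal the problem. With several SNPs, Cochran's Q can. Replication might, but the article gives no assay platform for the replication studies and does not present replication as a check on binding. RAPS also needs several SNPs, and it handles error in the estimated SNP effects, not a readout that depends on genotype.
- A reader might infer that forward MR alone settles direction or removes a protein from the biomarker list. The article says only that a forward association may suggest causality, and places MR among sensitivity analyses beside colocalization.
- Reverse MR, which serves the main aim, leaves out the protein's own cis-pQTLs.
- Protein-altering variants can carry valid information about level or function, so discarding them outright is not clearly better.

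It can also be said that variant annotation belongs to a fuller plan that is not shown. That carries less weight here. The article itself fixes the threshold, the window, the estimator for each SNP count and the cis exclusion for reverse MR. The rule as stated admits these variants, against the article's own statement about its assay.

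**Conclusion.** The point holds in a limited form. As written, forward MR admits every cis-pQTL that meets the p-value and distance criteria, while the article concedes that its assay reads binding. A protein-altering variant that changes binding and also affects level, function or cancer by another route can give a wrong sign or size per SD of level. In the assumed examples a true 0.20 becomes -0.30 or 0.60. One that changes binding only pulls the estimate to the null and can hide an upstream protein. Proteins with a single instrument are the most exposed, because no heterogeneity check exists, F is at least about 44, and colocalization cannot separate a binding effect from a level effect.

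The allele effects, the standard errors and the pQTL sample size are assumptions. The share of affected instruments cannot be computed from the document. The finding does not undermine the reverse-MR analysis or the main aim. It should be addressed because the remedy is cheap and the forward estimates will otherwise be read as effects of level.

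**What to change.** Annotate each cis-pQTL, and its close LD proxies, for protein-altering consequence. Pre-specify a sensitivity analysis that reports forward MR with and without those variants. Where the only instrument is protein-altering, or the two results disagree, flag the protein. For flagged proteins, do not interpret the sign or size as an effect of protein level, and do not treat a null as evidence against forward causation. Apply the same reading rule when Cochran's Q shows heterogeneity that is traced to such a variant.

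The all-cis result stays in the report, so valid information from protein-altering variants is not lost. The cost is a small annotation step with no new participant data, and some proteins will have a less definite forward-MR reading.
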